This protocol addresses a single-blind, 2-arm randomized controlled pilot study of an intensive lifestyle exercise and dietary intervention in PC patients undergoing prolonged ADT. The primary objective of the Intensive Diet and Exercise Adherence-Pilot (IDEA-P) trial is to determine the feasibility and preliminary efficacy of delivering a combined exercise and dietary counseling intervention to prostate cancer patients undergoing ADT. Preliminary data and effect size estimates obtained from this pilot study will be used as the foundation for the design of larger clinical exercise intervention studies in this priority population of prostate cancer patients. A total of 40 to 50 men undergoing ADT who plan to continue ADT for the next 3 months, will be randomly assigned to receive either the lifestyle exercise and dietary intervention (n=20-25) or standard of care disease management education (n=20-25). Assessment of all functional, anthropometric, and QOL outcomes will be obtained at baseline, after completion of the intervention at 2 months, at a follow-up visit 3 months following the baseline assessment, and at a final follow up visit scheduled between 6 and 8 months following baseline (see Figure 2: Study Design).

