**6. Research Approach and Design**

**Approach.** IDEA-P is a single-blind, 2-arm randomized controlled pilot study designed to determine the feasibility and preliminary efficacy of an intensive lifestyle exercise and dietary intervention in PC patients undergoing prolonged ADT. A total of 40-50 men undergoing ADT will be randomly assigned to receive either the lifestyle exercise and dietary intervention (n=20-25) or standard of care disease management education (n=20-25). Assessment of all functional, anthropometric, and QOL outcomes will be obtained at baseline, after completion of the intervention at 2 months, and at a follow-up visit 3 months following the baseline assessment (see Figure 2).

**
[figure not shown]
**

**6.1 Recruitment and Description of Human Subjects.** In collaboration with the OSUCCC and the

Genitourinary Oncology Disease Unit, [name] will serve as the focal point for recruitment of men for this study. His efforts in this capacity integrate the PC care for the OSUCCC and the JCH. [name] also manages a multimodality clinical effort each Wednesday at the JCH, where medical oncologists, radiotherapists, and urologists jointly manage patients. At the present time, well over 1,000 men with PC are referred to JCH each year. Under [name] direction, the OSU team has led the nation in annual number of local patient accrual to GU clinical trials among the nearly 50 participating institutions of the Cancer and Leukemia Group B (cooperative group) for the last 4 years. In 2009 and 2010 the OSU team has accrued over three times as many GU patients as any other CALGB institution. In addition, [name] research team has successfully met total accrual via local recruitment of PC patients in several investigator-initiated trials of NIH-NCI-funded diet and nutrition studies.

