**6.5 Methods for Both Arms (n = 40-50).** Men expressing an interest in the study will complete a brief screening interview to verify eligibility for inclusion in the trial. Men who meet the inclusion criteria can then sign the consent form during the clinic visit. Participants will complete the Dual-energy X-ray Absorptiometry (iDXA) scan anytime within one month of signing consent. The iDXA will be completed using the high definition GE Lunar iDXA. The iDXA machine is located in the gymnasium of Martha Morehouse, the same building at the Oncology Clinic. All other study visits will be conducted at the Recreation and Physical Activity Center on The Ohio State University main campus. **Please see the appendix for a detailed table of study visits**. At the baseline visit, the study will be explained in greater detail to the participant and all questions will be answered. The baseline visit will be comprised of anthropometric assessments, followed by the functional battery, and exercise and nutrition questionnaire assessments (the questionnaires can be completed at home if preferred by the participant) and finally randomization to either the Exercise and Diet Intervention arm or the Standard of Care arm. Participants will be given the option of completing the questionnaire assessments using the online RedCap data acquisition system. The OSU CCTS Research Informatics Services Core will be used as a central location for data processing and management. Vanderbilt University, with collaboration from a consortium of institutional partners (including OSU) and the NIH National Center for Research Resources, has developed a software toolset and workflow methodology for electronic collection and management of research and clinical trial data. REDCap (Research Electronic Data Capture) data collection projects rely on a thorough study-specific data dictionary defined in an iterative self-documenting process by all members of the research team with planning assistance from the CCTS Research Informatics Services Core. As part of the data dictionary development process, individual fields can be denoted as “identifiers”. When exporting a de-identified dataset, these variables are omitted. Additionally, the data export tool also allows for the shifted of dates for a limited data set export. REDCap provides a secure, web-based application that is flexible enough to be used for a variety of types of research, provides an intuitive interface for users to enter data and has real time validation rules (with automated data type and range checks) at the time of entry. It offers easy data manipulation with audit trails and ad hoc reporting functionality for reporting, monitoring and querying patient records, and an automated export mechanism to common statistical packages (SPSS, SAS, Stata, R/S-Plus). REDCap is 21 CRF Part 11 capable. Currently, REDCap installations support electronic signatures by positively identifying the user through a unique username and password combination. The provisioning of accounts and user access to specific database(s) is integrated with the OSU Medical Center LDAP authentication service, and the provisioning of access and specific user rights are managed by CCTS staff. The use of this technology will streamline subject visits and provide the capacity for precoding research data for export and analysis. Participants will be provided verbal and written instructions on how to wear the objective physical activity monitor (LIFECORDER Plus accelerometer) and will wear it for the next 7-days. Monitors will be returned to trial staff via U.S. postal service. Participants will return for three additional assessment visits: two months after baseline, three months after baseline, and between six and eight months after their baseline visits, and assessments identical to that at baseline will be obtained. Assessment of all functional, anthropometric, and QOL outcomes will be obtained at baseline by project staff who are blinded to participants’ treatment arm assignment.

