
- *Self-monitoring*: develop awareness and commitment to tracking/recording of desired exercise and dietary behaviors
- *Goal-setting*: Setting short and long-term, process and outcome-related goals for target exercise and dietary behaviors
- *Stimulus Control*: Development of appropriate behavioral, environmental, and reinforcement strategies that help to facilitate adoption and maintenance of change in exercise and dietary habits (e.g., appropriate exercise pacing, providing oneself with exercise and dietary reminders, identifying appropriate rewards for reaching desired exercise and dietary goals, developing healthier grocery shopping/cooking strategies)
- *Barrier problem-solving*: Use of a social problem-solving approach to identify, practice, and implement self and peer-initiated strategies for overcoming common barriers to exercise and dietary behavior.
- *Cognitive restructuring*: Develop a more positive orientation towards exercise and healthy eating (e.g., monitoring affect during exercise to optimize affect/enjoyment, motivational interviewing to identify positive motives and attitudes for changing exercise and dietary behavior).

**Methods for the Standard of Care Intervention Arm (n = 20-25).** Men randomized to the standard of care arm will receive usual PC treatment as well as educational literature describing the American Institute of Cancer Research dietary and physical activity guidelines. To equate contact between treatment arms to levels consistent with similar, contemporary lifestyle intervention trials (32, 38), 20-min phone contacts delivered by [name] clinic staff focusing on routine aspects of PC self-management will be conducted biweekly with men in the standard of care arm. As an incentive to promote retention across the trial, men randomized to standard of care will also receive 2 supervised exercise training sessions and dietary counseling sessions following the completion of the 3 month assessment. Men will complete assessments of all outcomes scheduled at baseline and months 2, and 3.

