**8. Statistical Considerations.**

Significance tests for the efficacy of the lifestyle intervention on the longitudinally gathered data at 2 and 3 months will be individually standardized by baseline values and will be evaluated using a weighted, repeated-measures analysis of variance statistical model adjusting for the effect of age. The primary aim is to estimate effect sizes for a future application. Although the sample size of 40-50 men does not provide optimal statistical power to detect treatment effects, it is feasible sample to recruit given the time and resources provided by the funding mechanism that, while accounting for a 20% attrition rate, would allow for adequate assessment of the feasibility of the intensive lifestyle intervention and obtain the effect size estimates necessary for the design of a large randomized controlled lifestyle intervention trial. Analyses will be conducted using the intention to treat principle with last value carried forward approach used to account for data missing due to participant attrition. Descriptive statistics for the feasibility measures will be calculated prospectively throughout the trial. Exploratory analyses of the direct and indirect pathways of the intervention effects on change in FL and QOL will be conducted using a structural equation modeling longitudinal panel model approach (AMOS 6.0 software; 66, 67). Panel models are ideal for analysis of hypothesized, theory-based relationships across defined periods of time. Again, while the sample size of 40-50 men is not optimal for panel analyses, it is sufficient to obtain estimates of path coefficients necessary to calculate the sample size in order to design an intervention trial that will be appropriately powered to detect meditational pathways of interest.

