**10. Risks and Benefits**

**Risks**: The risks associated with this protocol are expected to be modest. Participants will complete functional and strength testing that has been shown to be of minimal risk of injury or physical discomfort. Men with any medical conditions that would increase the risk of completing these tests or participating in regular, personalized moderate intensity exercise will be excluded from participation. Any physical injury or discomfort will be infrequent, mild, and should not have any long-term effects. To ensure participant safety, all testing and exercise sessions will be conducted under the supervision of an experienced exercise and fitness professionals who is CPR-certified.

As for risk associated with the iDXA scan, additional ionizing radiation has the potential to damage proteins in the body, including DNA, as well as contribute to the subject’s accumulated radiation over time. There are no common adverse effects from bone densitometers and concern is limited to the overall accumulated radiation of each subject.

**Confidentiality:** Patient confidentiality of records will be maintained. Individuals will not be identified by name or by any other personal identifying information in laboratory records, reports, or publications resulting from this study. Thus, risk of disclosure of confidential medical information will be essentially nonexistent. Additionally, all data will be number coded and stored in a locked research office that can only be accessed by the research staff. These procedures have been successfully used to protect confidentiality in both [name] and [name] prior completed research.

**Benefits**: The benefits to the participant are significant. Men enrolled in the diet and exercise arm may improve their fitness over the course of the three month study. Men may feel more energetic, confident and activities of daily living may be easier. Additionally, the combination of diet and exercise counseling may facilitate weight loss in men who are overweight which can result in improved health and self image. All men who participate in this clinical trial will potentially have feelings of self-satisfaction for having contributed toward scientific understanding of prostate cancer treatment. Additionally, we will provide a $25 cash incentive for the completion of each major assessment visit (baseline, month 2, month 3, and month 6-8) for a total of $100 for study completion.

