**Study Schedule for Standard-of-Care Group**

|  |  | |  | **Month 1** | | | | **Month 2** | | | | **Month 3** | | | | **Months 6-8** |
| --- | --- | --- | --- | --- | --- | --- | --- | --- | --- | --- | --- | --- | --- | --- | --- | --- |
|  | **Oncology**  **Clinic Visit** | | **Baseline and Randomization** | **Week**  **1** | **Week**  **2** | **Week**  **3** | **Week**  **4** | **Week**  **5** | **Week**  **6** | **Week**  **7** | **Week**  **8** | **Week**  **9** | **Week**  **10** | **Week**  **11** | **Week**  **12** | **Weeks 24-32** |
| **Sign Consent** | **x** | |  |  |  |  |  |  |  |  |  |  |  |  |  |  |
| **iDXA Scan** | **x** | |  |  |  |  |  |  |  |  |  |  |  |  | **x** |  |
| **Physical Assessment**  **(*functional and strength battery, anthropometric measures)*** |  | | **x** |  |  |  |  |  |  |  | **x** |  |  |  | **x** | **x** |
| **Phone Contact regarding PCa care** |  | |  |  | **x** |  | **x** |  | **x** |  | **x** |  | **x** |  | **x** |  |
| **Quality of Life Questionnaires** |  | | **x** |  |  |  |  |  |  |  | **x** |  |  |  | **x** | **x** |
| **Behavioral & Feasibility Questionnaires** |  | | **x** |  |  |  |  |  |  |  | **x** |  |  |  | **x** | **x** |
| **National Institutes of Health FFQ and Fruit & Vegetable Screener** |  | | **x** |  |  |  |  |  |  |  |  |  |  |  | **x** | **x** |
| **Three Day Diet Records** | |  | **x** |  |  |  |  |  |  |  |  |  |  |  | **x** | **x** |

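### The protocol ends assessment at month 3 in some sections and at months 6–8 in others, and its timeline has room only for the shorter version

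*Protocol*

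**What the plan says.** **Places that stop at month 3**

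- Section 6, Approach paragraph (both arms): assessments at baseline, "after completion of the intervention at 2 months, and at a follow-up visit 3 months following the baseline assessment". Nothing later is listed.
- Section 6.5, standard-of-care arm: "Men will complete assessments of all outcomes scheduled at baseline and months 2, and 3".
- Section 10, Benefits, describes gains in the lifestyle arm "over the course of the three month study".
- Section 11: recruitment runs from month 4 of Year 1 through month 7 of Year 2, and data collection ends in month 10 of Year 2.

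**Places that include months 6–8**

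- Section 1, Study Overview: the assessments finish "at a final follow up visit scheduled between 6 and 8 months following baseline".
- Section 6.5, Methods for Both Arms: three return visits, "two months after baseline, three months after baseline, and between six and eight months after their baseline visits".
- Section 10 pays for four visits ("baseline, month 2, month 3, and month 6-8) for a total of $100 for study completion") without distinguishing the arms.
- Appendix: both schedules, including the one titled "Study Schedule for Standard-of-Care Group", mark physical assessment and questionnaires at weeks 24–32.

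**Places that depend on the answer**

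- Section 3, Objective 2, hypothesises acceptable retention. Section 7 lists retention as a feasibility measure, described as the trial proceeds, with no visit named.
- Section 8 justifies 40–50 men "while accounting for a 20% attrition rate". Section 6.1 calls even a 20% loss tolerable. Neither names a visit.
- Section 8 places the efficacy tests at months 2 and 3.

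**The concern.** All of this is operative text, and section 6.5 disagrees with itself: its both-arms paragraph sends every participant to a months 6–8 visit, while its standard-of-care paragraph stops control men at month 3. Staff working from the arm-specific paragraph could close out a control man at month 3. Staff working from the appendix would count the same man as missing if he did not attend at weeks 24–32.

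Feasibility is part of the trial's primary objective, and retention is one of the few measures that speak to it. If the two arms are followed to different ends, final retention cannot be compared between them, and anything measured at months 6–8 in the lifestyle arm lacks a concurrent control. Separately, if the section 11 dates are kept, late enrolees would miss the final visit because the study has closed. That is administrative loss, yet it would look like poor retention.

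**Working it through.** **1. Which last visit applies to whom**

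| Place | Lifestyle arm | Standard-of-care arm |
| --- | --- | --- |
| Section 1 | months 6–8 | months 6–8 |
| Section 6, Approach | month 3 | month 3 |
| Section 6.5, both arms | months 6–8 | months 6–8 |
| Section 6.5, standard of care | not addressed | month 3 |
| Section 10, payments | months 6–8 | months 6–8 |
| Appendix schedules | months 6–8 | months 6–8 |

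Following section 6 throughout, or the appendix throughout, gives equal follow-up. Combining the standard-of-care paragraph for controls with the appendix for the lifestyle arm gives 3 months against 6–8 months.

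**2. Whether the timeline can hold the later visit**

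Inputs (section 11): recruitment ends in project month 12 + 7 = 19; data collection ends in month 12 + 10 = 22; the project lasts 24 months.

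- Gap: 22 − 19 = 3 months, exactly enough for a month-3 last visit.
- The last man enrolled would reach his final visit in month 19 + 6 = 25 to 19 + 8 = 27, after data collection and after the project. Using the spare time to month 24 does not rescue this.
- Latest enrolment for a visit by month 22: 22 − 6 = month 16 for the start of the window, and 22 − 8 = month 14 for the whole window.

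Number of men affected, *assuming* even accrual over months 4–19 (16 months):

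- Months 17–19: 3/16 = 19%, which is 7.5 of 40 or 9.4 of 50 men who cannot reach even the start of the window.
- Months 15–19: 5/16 = 31%, which is 12.5 of 40 or 15.6 of 50 men without the full window.

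This depends on accrual. At the upper target of 5 men per month, 50/5 = 10 months, so recruitment would close in month 13 and every 8-month visit would fall by month 13 + 8 = 21. At 3 per month, 40/3 = 13.3 months runs into month 17, and the clash arises.

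**3. What the 20% allowance implies**

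The 40–50 is justified by feasibility. No power, effect size or required number of completers is stated, so there is no calculation to reproduce. The allowance itself gives 40 × 0.8 = 32 and 50 × 0.8 = 40 men, or 16–20 per arm, at whichever visit it refers to.

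If 20% are lost by month 3, loss at the final visit depends on what happens afterwards:

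| Assumption after month 3 | Loss at final visit | Left per arm (of 20–25) |
| --- | --- | --- |
| No further dropout | 20% | 16–20 |
| Constant rate, visit at month 6 | 1 − 0.8^(6/3) = 36.0% | 12.8–16.0 |
| Constant rate, visit at month 8 | 1 − 0.8^(8/3) = 44.8% | 11.0–13.8 |

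If instead the 20% was meant for the final visit, the constant-rate assumption gives 1 − 0.8^(3/6) = 10.6% (visit at month 6) or 1 − 0.8^(3/8) = 8.0% (visit at month 8) lost by month 3. The constant rate is an assumption made here; the protocol gives no dropout pattern.

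**The case against.** The best defence is that the months 6–8 visit is plainly intended and that the month-3 sentences are merely incomplete. The both-arms paragraph of section 6.5 refers the reader to the appendix for detail, the control-specific appendix schedule marks weeks 24–32, and payment is offered to everyone. The standard-of-care paragraph does not say that month 3 is final. This makes unequal follow-up a risk, not a likely outcome. But that paragraph is the arm-specific instruction, and it also offers controls exercise and dietary sessions after the 3-month assessment as a retention incentive across the trial, which reads as if month 3 were the end. The section 11 dates cannot be explained as an incomplete list. The reference in section 10 to a three-month study is weaker evidence, since it may mean the intervention period.

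It is also fair to say that retention is descriptive, is tracked throughout and has no threshold, and that its exact definition may sit in an analysis plan. That stands: the missing visit label is secondary, and the schedule contradiction is the defect.

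A reader might infer more: that retention and the 20% allowance refer to different follow-up lengths, so that the allowance can be true at only one visit. The documents do not support this. Neither is given any length. The 20% is worded as a tolerable level, and a loss of at most 20% by month 8 implies at most 20% by month 3, so it can hold at both. Nor does the protocol claim that the sample is adequate for the months 6–8 data specifically.

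**Conclusion.** The contradiction is real and should be resolved. Its consequences are confined to the final visit: whether controls are assessed then, whether final retention is comparable between arms, and whether late enrolees can attend before data collection closes. The month 2 and month 3 efficacy tests are not affected.

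The timeline conflict follows from the protocol's own dates: 3 months are available where 6–8 are needed for the last man enrolled. The share of men affected (roughly 19–31%) rests on even accrual to the planned end of recruitment and would be nil at the upper accrual target. Loss at the final visit, given 20% at month 3, would be at least 20%; the 36–45% figures (about 11–16 men left per arm) rest entirely on an assumed constant dropout rate and breach no stated requirement.

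**What to change.** 1. Give both arms the same last visit everywhere. If the months 6–8 visit stands, as the Study Overview, the both-arms paragraph of section 6.5, the payment schedule and both appendix schedules have it, amend the Approach paragraph of section 6, the standard-of-care paragraph of section 6.5 and the study-length wording in section 10 to match.
2. Change section 11 so that it can hold that visit, by closing recruitment earlier (by project month 14 for the full window) or extending data collection (to month 27 if recruitment runs to month 19).
3. Report retention among all randomised men, by arm, at month 3 and separately at months 6–8, distinguishing men who dropped out from men whose visit fell after data collection closed.
4. State in section 8 that the 20% allowance refers to month 3, the last visit analysed there, and that loss at months 6–8 will be at least as large.

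The cost is mostly wording, with no visits beyond those already in the appendix. The timeline change is the substantive part, since it shortens recruitment or lengthens the project. Final-visit retention may also look less favourable than a month-3 figure.
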